# Endometrial ablation plus levonorgestrel releasing intrauterine system versus endometrial ablation alone in women with heavy menstrual bleeding: study protocol of a multicentre randomised controlled trial; MIRA2 trial

**DOI:** 10.1186/s12905-022-01843-6

**Published:** 2022-06-27

**Keywords:** Heavy menstrual bleeding, Dysmenorrhoea, Endometrial ablation, Hysterectomy, Levonorgestrel-releasing intrauterine system, Pelvic pain

## Abstract

**Background:**

It is estimated that between 12 to 25% of women who undergo an endometrial ablation for heavy menstrual bleeding (HMB) are dissatisfied after two years because of recurrent menstrual bleeding and/or cyclical pelvic pain, with around 15% of these women ultimately having a hysterectomy. The insertion of a levonorgestrel-releasing intrauterine system (LNG-IUS) immediately after endometrial ablation may inactivate residual untreated endometrium and/or inhibit the regeneration of endometrial tissue. Furthermore, the LNG-IUS may prevent agglutination of the uterine walls preventing intrauterine adhesion formation associated with endometrial ablation. In these ways, insertion of an LNG-IUS immediately after endometrial ablation might prevent subsequent hysterectomies because of persisting uterine bleeding and cyclical pelvic pain or pain that arises de novo. Hence, we evaluate if the combination of endometrial ablation and an LNG-IUS is superior to endometrial ablation alone in terms of reducing subsequent rates of hysterectomy at two years following the initial ablative procedure.

**Methods/design:**

We perform a multicentre randomised controlled trial in 35 hospitals in the Netherlands. Women with heavy menstrual bleeding, who opt for treatment with endometrial ablation and without contraindication for an LNG-IUS are eligible. After informed consent, participants are randomly allocated to either endometrial ablation plus LNG-IUS or endometrial ablation alone. The primary outcome is the hysterectomy rate at 24 months following endometrial ablation. Secondary outcomes include women’s satisfaction, reinterventions, complications, side effects, menstrual bleeding patterns, quality of life, societal costs.

**Discussion:**

The results of this study will help clinicians inform women with HMB who opt for treatment with endometrial ablation about whether concomitant use of the LNG-IUS is beneficial for reducing the need for hysterectomy due to ongoing bleeding and/or pain symptoms.

*Trial registration* Dutch Trial registration: NL7817. Registered 20 June 2019, https://www.trialregister.nl/trial/7817.

**Supplementary Information:**

The online version contains supplementary material available at 10.1186/s12905-022-01843-6.

## Background

Heavy menstrual bleeding (HMB) is a common problem affecting one in four women between 30 and 50 years of age, with serious implications on quality of life and social functioning [1]. Endometrial ablation (EA) is a common minimally invasive, surgical treatment for women suffering from HMB. In the Netherlands, around 6000 EA-procedures are performed per year. EA is a uterus-preserving procedure that aims to destroy the endometrium, thus reducing or stopping menstrual bleeding [2]. However, approximately one in five women is dissatisfied after EA because of ongoing vaginal bleeding and/or dysmenorrhoea and seek further treatment [3–7]. A recent study by Beelen et al. showed that 20% of all women treated with EA received reinterventions and 10% ultimately underwent a hysterectomy [3]. Ongoing vaginal bleeding results from untreated or regenerated endometrium. Post-treatment dysmenorrhoea is likely the result of bleeding from areas of untreated or regenerated endometrium into a scarred and partially obliterated uterine cavity, causing a hematometra. Another cause is the presence of ectopic endometrial tissue within the underlying myometrium, known as adenomyosis [8–11].

Insertion of a levonorgestrel-releasing intrauterine system 52 mg (LNG-IUS, Mirena^®^, Bayer HealthCare Pharmaceuticals, Germany) immediately after EA may prevent persisting HMB and dysmenorrhoea. The local release of progesterone can potentially inactivate non-ablated or inhibit the regeneration of endometrial tissue as well as endometrial glands within the myometrium, thereby suppressing pelvic pain caused by adenomyosis [8, 12]. The LNG-IUS may also prevent intrauterine adhesion formation, which reduces the chance to develop hematometra. Uterine cavity obliteration developing in the period after EA mostly precludes later re-ablation or insertion of an LNG-IUS, often resulting in the preference for hysterectomy in case of discontent with the results of EA [9, 13].

A recently published systematic review concluded that combined EA + LNG-IUS treatment is a safe and promising procedure with a substantial lower reintervention and hysterectomy rate compared to treatment with EA alone [14]. A retrospective, single-centre cohort of 82 women in the study of Zhao et al. (2020) showed that women who received the combined treatment had a 0% hysterectomy rate compared to a 12% hysterectomy rate in women who received EA alone within a follow up period of 24 months [15]. In another retrospective single centre cohort of 88 women having EA combined with LNG-IUS, there was a 24% reduction in hysterectomy rate over a mean follow-up of 36 months [16]. Complication rates from combined treatment do not appear to be higher than treatment with EA alone [14].

Hence, in light of the potential benefits of combining EA and LNG-IUS and the availability of observational studies only [14], rigorous evaluation in a large multicentre randomised controlled trial (RCT) is essential. The MIRA2 trial will assess the effectiveness and cost-effectiveness of EA in combination with an LNG-IUS in comparison with EA alone in women with HMB using the rate of hysterectomy as the primary outcome measure.

## Methods/design

### Objective

The aim of this study is to assess whether the insertion of an LNG-IUS directly after EA is more effective in reducing the need for subsequent hysterectomy within two years of the EA in women with HMB and undergoing EA, as compared to EA alone. Also, the study will evaluate women’s satisfaction, reinterventions and complications, side effects, post-ablation menstrual bleeding patterns, quality of life, sick leave, and costs-effectiveness.

### Study design

The MIRA2 study is a nationwide multicentre randomised controlled clinical trial (RCT) in the Netherlands investigating the superiority of EA combined with concurrent LNG-IUS compared over EA alone. An economic evaluation will be performed alongside the trial. The study will be performed within the infrastructure of the Dutch Consortium for studies in Women’s Health. This study will be conducted in accordance with the Declaration of Helsinki as well as the Netherlands Medical Research Involving Human Subjects Act (WMO) and was approved as a primary review by the Máxima Medical Center medical ethics committee. Trial registration is available in the Dutch Trial Register (NL7817).

A complete overview of the MIRA2 trial is presented in Fig. 1.

**Fig. 1 Fig1:**
[figure not shown]
Flowchart of the MIRA2 trial. HMB = Heavy Menstrual Bleeding, CRF = Case Report Form, LNG-IUS = Levonorgestrel Intra-uterine system, EQ-5D-5L = The 5-level EuroQol version of quality-of-life questionnaire, MMAS-Shaw = menorrhagia multi-attribute scale questionnaire, PBAC = Pictorial Blood Loss Assessment Chart, iMCQ = iMTA Medical Consumption Questionnaire, iPCQ = iMTA Productivity Cost Questionnaire, SAE = Serious Adverse Event

### Study population

Women suffering from HMB who opt for treatment with EA can participate in the trial. Women with contraindications for use of LNG-IUS are excluded from the trial. Other exclusion criteria are age of 60 years or older, suspicion of endometrial cancer and prior endometrial ablation. Moreover, women who are unable to read or speak Dutch or English to a level that allows them to fully understand the study description and informed consent cannot participate in the trial.

### Participants recruitment, randomisation and collection of data

Participants meeting the eligibility criteria will be counselled about the study by their physician or a research nurse, who will provide them with written information about the study. Women will be counselled according to the ‘shared decision making’ principle. Women who agree to participate in the study must provide written informed consent before randomization can take place by a research nurse or researcher.

Randomisation will be stratified by the presence of pre-existing dysmenorrhoea at baseline (pain during menstruation for which most of the menstrual periods pain medication is necessary) and by age (under and above 45 years old). Variable block sizes of size 2, 4 and 6 will be used.

The online software tool Castor EDC (www.castoredc.com) will be used for randomisation, sending questionnaires, and data collection. The computer will randomly assign a unique numeric code for every subject, consisting of the hospital and the consecutive participant number. A coded data set will be handled, and only the local investigator and the research nurse on site will have access to the key (code to personal information linkage). These coded data are available to investigators, research staff, and quality assurance and monitoring personnel. After the study is complete, data will be archived for a period of 15 years. Personal data is handled in compliance with the EU General Data Protection Regulation and the Dutch Act on Implementing the General Data Protection Regulation.

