#### Electronic case report form for researchers

Baseline demographic characteristics, medical history, pre-existing dysmenorrhoea and current use of hormonal medication are recorded by the physician/research nurse in the electronic CRF. In addition, findings of the ultrasound examination will be collected in the eCRF, specifically, the existence of myomas (number, type and size) and presence of possible signs of adenomyosis.

At 6 weeks and 24 months after intervention the research nurse/physician will record post-treatment complications (expulsion or removal IUS, endometritis, uterine infection, bleeding (> 500 ml), uterine perforation caused by IUS insertion or EA) and reinterventions (including hysterectomy, removal of IUS, re-ablation or medical treatment).

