## Statistical analysis

### Sample size

Based on a literature search of previous studies on hysterectomy rate after EA, we found variation in hysterectomy rates between 9 and 17.5% [3, 23–26]. An assessment in the Dutch population of hysterectomy rates after EA indicates a hysterectomy rate around 15% after previous EA in daily practice. For the sample size calculation, we assume a 15% hysterectomy rate after treatment with EA alone.

Based on a literature search on treatment with EA and LNG-IUS, we found two recently published studies with a comparable study population [15, 27]. These studies show hysterectomy rates after combined treatment between 0 and 11%. Therefore, in this study the hysterectomy rate in the group treated with EA and LNG-IUS is hypothesized to be 8% [15, 27]. Using an alpha of 0.05 and a beta of 0.2 and the 15% hysterectomy rate in the EA alone group and 8% in the EA + LNG-IUS group, 646 participants are needed to achieve 80% power. This enables the detection of a 7-percentage point’s difference between the group proportions. The sample size was calculated using the two-sided Z-Test with unpooled variance. Assuming a 10% loss-to-follow-up rate, we need to recruit 718 participants in the trial (359 per group). This sample size calculation was performed using PASS15.0.10.

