### Subgroup analysis

Subgroup analyses will be conducted for women with pre-existing dysmenorrhoea, women with tubal ligation as contraception and for women under and over 45 years of age. Subgroup effects will be studied using interaction terms in a generalised linear model.

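### The age effect on treatment is described only through a split at 45 years; adding a treatment-by-continuous-age term would recover information at little cost

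*Protocol article*

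**What the plan says.** All references are to the protocol article.

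- **Participants recruitment, randomisation and collection of data:** two stratification factors are set. "Randomisation will be stratified by the presence of pre-existing dysmenorrhoea at baseline", and the second factor is age, given as "and by age (under and above 45 years old"). Randomisation runs in Castor EDC.
- **Subgroup analysis:** one of the planned analyses is "for women under and over 45 years of age". The method is stated: "Subgroup effects will be studied using interaction terms in a generalised linear model".
- **Study population:** "Other exclusion criteria are age of 60 years or older". No lower age limit is given.
- **Electronic case report form for researchers:** "Baseline demographic characteristics, medical history, pre-existing dysmenorrhoea and current use of hormonal medication are recorded". Age is not named, but the age limit and the stratum cannot be applied without it.
- **Data-analysis:** the primary analysis is a relative risk with a chi-squared test in the intention-to-treat population. As described, it does not use age.

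**The concern.** Whether the benefit of adding the LNG-IUS changes with age is one of the few effect-modification questions that the trial names in advance. As described, it is answered by comparing two age groups. Such a comparison treats a woman of 35 like one of 44, and a woman of 46 like one of 58. If the effect shifts gradually with age, the variation inside each group carries information that the test ignores.

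Interaction tests have little power in a trial sized for a main effect, so a further loss matters to anyone who reads a non-significant age interaction as evidence of a uniform effect. The stake is the sensitivity of this one subgroup analysis.

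A smaller wording point sits beside it: neither section says in words which group contains a woman aged 45.

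**Working it through.** **1. The plan's own figure.** Inputs from the Sample size section: 15% and 8% hysterectomy, two-sided alpha 0.05, beta 0.2, Z-test with unpooled variance, 10% loss to follow-up.

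- Variance sum: 0.15 × 0.85 + 0.08 × 0.92 = 0.2011.
- n per arm = 0.2011 × (1.960 + 0.842)² / 0.07² = 322.1, rounded up to 323; total 646.
- 323 / 0.90 = 358.9, rounded up to 359; total 718.

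Both stated totals are reproduced. Neither depends on the age cut.

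**2. What the split can detect.** Take 646 evaluable women, equal age halves and the planning variances in each half (an illustration). Each treatment-by-age cell then has 646 / 4 = 161.5 women. The standard error of the difference between the two risk differences is √(2 × 0.2011 / 161.5) = 0.0499.

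- A 14-point difference between the age groups in risk difference: power 80%.
- A 7-point difference: power 29%.

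**3. Information kept by the split.** When the effect modification is linear in age, age is normal and the outcome variance is roughly constant over age, the information kept by a cut at c, relative to continuous age, is

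φ(z)² / [p(1 − p)], with z = (c − mean)/SD and p the share above the cut.

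The documents give no age distribution, so the mean and SD below are assumptions.

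| Mean | SD | z | φ(z) | p | Information kept |
|---|---|---|---|---|---|
| 43 | 5 | 0.40 | 0.368 | 0.345 | 60% |
| 44 | 5 | 0.20 | 0.391 | 0.421 | 63% |
| 45 | 5 | 0.00 | 0.399 | 0.500 | 64% |
| 46 | 5 | −0.20 | 0.391 | 0.579 | 63% |
| 43 | 6 | 0.33 | 0.377 | 0.369 | 61% |

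With SD 6 and means 44–46 the result is 63–64%. The ceiling for normal age, reached when the cut is at the mean, is 2/π = 64%. A mean further from 45 does worse: mean 42 with SD 5 gives 56%.

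**4. In terms of power.** Take a linear trend that the continuous test would detect with 80% power, so that its expected test statistic is 1.960 + 0.842 = 2.802. The split reduces this by the square root of the information kept.

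- 60%: 2.802 × √0.60 − 1.960 = 0.21, power about 58%.
- 64%: 2.802 × √0.64 − 1.960 = 0.28, power about 61%.

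**5. The boundary at 45.** If age is taken in completed years and both age groups are read strictly, the women in neither group are those from their 45th to their 46th birthday. Under the same assumed distributions they are 6–8% of the sample, about 44–57 of 718. If age is exact, the cut falls at the 45th birthday and almost nobody is affected. Even if 5–8% were dropped from the subgroup analysis, the power figures in step 2 would fall only from 80% to 77–78% and from 29% to 27–28%.

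**The case against.** The case against acting has four parts.

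- **The binary cut is a legitimate pre-specified choice.** It matches a stratification factor and is tested with a formal interaction term. This stands, and it is why the split should stay.
- **A continuous-age analysis may already exist** in the full protocol or the statistical analysis plan, neither of which is shown. This also stands. The article does not say that age will be analysed in no other way; the split is only the sole age analysis that it describes.
- **The efficiency figure depends on a linear trend and an assumed age distribution.** This is correct. If the effect changed sharply near 45, the 60–64% would not apply and the split could be the better test. That argues for having both analyses, not for relying on either alone.
- **The consequence is small.** This is correct too: the primary analysis and the sample size are untouched.

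A reader might go further and infer from the wording that women aged 45 have no stratum, that hospitals could place them differently, or that they drop out of the subgroup analysis. The documents do not support this. A stratified electronic system has to put each woman in a stratum before it allocates her. The article does not say that sites choose the stratum. An exact-age reading leaves almost nobody out. What remains is a detail of wording that a condensed article may leave to its full protocol.

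**Conclusion.** The point holds as an inexpensive improvement. The article describes age as an effect modifier only through the 45-year split, while age must already be known for eligibility and stratification. If the treatment effect changes roughly linearly with age, the split keeps about 60–64% of the information on that interaction, as if more than a third of the sample were set aside for this test. The figure rests on assumed normal ages with mean 43–46 and SD 5–6 years and on linearity; none of these is in the documents. Importance is low and confined to one subgroup question. The unassigned age of 45 is an editorial matter.

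**What to change.** - In the generalised linear model of the Subgroup analysis section, pre-specify a treatment-by-continuous-age interaction, with age itself as a main effect. State in advance that this term carries the test of the age trend.
- Keep the 45-year split alongside it for display, with each woman in the stratum actually used for her in Castor.
- As an editorial correction, say in both the randomisation and the subgroup sections on which side age 45 falls, as programmed in Castor.

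The cost is one interaction term with its main effect and a few words in two places. It needs no new data, provided that age is held in the database as the age limit and stratum imply. The downside is that the continuous test assumes a roughly linear trend, which is a further reason to report the split beside it. If the analysis plan already contains such a term, only the wording correction remains.

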### Interventions

Hospitals using electrical, radiofrequency ablation (Novasure^®^, Hologic, Marlborough, MA, USA), the thermal balloon ablation (Thermablate^®^, Idoman Teoranta, Ireland and Librata^®^, Lina Medical, Denmark) or transcervical resection of the endometrium can participate in this trial. Hospitals performing this procedure must conduct a minimum of 15 procedures a year to assure quality and competency. The EA procedure may be performed under local anaesthesia in the outpatient office, under conscious sedation in an outpatient clinic or under general or spinal anaesthesia in an operating room, depending on the local conditions in the respective centre. In women allocated to EA + LNG-IUS, an LNG-IUS will be inserted immediately after finishing the EA procedure. The LNG-IUS can stay in place for a maximum of five years in case contraception is needed or longer in case contraception is not needed. Women allocated to the control group, only an EA will be performed.

### Outcome measures

The primary outcome will be the hysterectomy rate at two years after endometrial ablation as treatment for HMB. This will be measured using questionnaires in the follow-up period and checked by consulting the individual participant file. Secondary outcomes will include women’s satisfaction (on a 6-point Likert scale), condition-specific quality of life and general Quality of Life, severity of cyclical and non-cyclical pelvic pain, presence of (inter)menstrual bleeding, non-hysterectomy reintervention rates (removal LNG-IUS, medical or other surgical interventions), number and type of complications and adverse effects of treatment. Costs will be evaluated from a societal perspective. Outcomes will be collected via an online questionnaire completed by participants and via an online Case Report Form (CRF) completed by researchers.

#### Questionnaires for participants

Prior to treatment, participants will be asked to complete a baseline questionnaire containing a validated condition-specific quality of life measure Menorrhagia Multi-Attribute Scale (MMAS) as well as a validated EuroQol 5-level questionnaire [17–19]. The English language version of the MMAS questionnaire is shown in Additional file 1. Also, menstrual blood loss with a written Pictorial Blood Loss Assessment Chart (PBAC) score will be measured at baseline (Additional file 2) [20]. Participants will complete a questionnaire at six months follow-up asking about contraceptive use and smoking habits (Additional file 3). At 6-, 12- and 24-months participants will receive a questionnaire containing the MMAS questionnaire, the EQ-5D-5L questionnaire, and PBAC scoring, and questions on women’s satisfaction (6-point Likert scale), side effects of the LNG-IUS, and the presence of cyclic pelvic pain (pain score 0–10).

Societal costs (healthcare costs, lost productivity costs and informal care costs) are assessed using specifically adapted versions of the iMTA Productivity Cost Questionnaire (iPCQ) and the iMTA Medical Consumption Questionnaire (iMCQ) at 6, 12, 18 and 24 months (Additional file 4) [21, 22]. Participants will be asked to complete a menstrual calendar for one month to evaluate the intermenstrual bleeding 24 months after treatment (Additional file 5). An overview of questionnaires and timepoints is shown in Table 1.

**Table 1 Tab1:** Schematic overview of follow up questionnaires for participants

Timepoints	T_0_: Baseline	T_2_: 6 months	T_3_: 12 months	T_4_: 18 months	T_5_: 24 months
1. 6 months follow up questionnaire		x			
2. Women’s satisfaction		x	x		x
3. EQ-5D-5L	x	x	x		x
4. PBAC	x	x	x		x
5. Cyclic pelvic pain and MMAS	x	x	x		x
6. Side-effects or complications		x	x		x
7. iMCQ and iPCQ		x	x	x	x
8. Menstrual calendar					x

EQ-5D-5L = The 5-level EuroQol version of quality-of-life questionnaire, PBAC = Pictorial Blood Loss Assessment Chart, MMAS = menorrhagia multi-attribute scale questionnaire, iMCQ = iMTA Medical Consumption Questionnaire, iPCQ = iMTA Productivity Cost Questionnaire

#### Electronic case report form for researchers

Baseline demographic characteristics, medical history, pre-existing dysmenorrhoea and current use of hormonal medication are recorded by the physician/research nurse in the electronic CRF. In addition, findings of the ultrasound examination will be collected in the eCRF, specifically, the existence of myomas (number, type and size) and presence of possible signs of adenomyosis.

At 6 weeks and 24 months after intervention the research nurse/physician will record post-treatment complications (expulsion or removal IUS, endometritis, uterine infection, bleeding (> 500 ml), uterine perforation caused by IUS insertion or EA) and reinterventions (including hysterectomy, removal of IUS, re-ablation or medical treatment).

